### **Secondary Outcomes:**

The efficacy and safety of SCT and continuous ART will also be compared through the analysis of HIV-1 viral load and T cell subsets measured locally at each protocol visit, the presence of mutations conferring resistance to drugs taken at randomisation or during the trial, changes in the stage of a young person's HIV disease (CDC classification – see Appendix 8) measured at trial entry and each protocol visit, and the presence of adverse events. To assess the advantages and disadvantages of the strategy, acceptability, quality of life and adherence to the randomised strategy will also be compared. Specifically, the secondary outcomes of the trial are:

- HIV-1 RNA  $< 50$  c/ml at 24 and 48 weeks.
- Number of HIV mutations present at week 4, 12, 24, 36 or 48 conferring resistance to drugs taken at randomisation or during the trial
- Change in CD4 (absolute and percentage) from randomisation to 24 and 48 weeks
- Change in ART (defined as any change from the ART regimen at randomisation)
- Grade 3 or 4 clinical and laboratory adverse events.
- ART treatment modifying adverse events (all grades).
- New CDC stage B or C diagnosis or death
- Changes in fasting glucose, cholesterol, triglycerides, LDL, HDL and VLDL levels through 48 weeks
- Adherence, acceptability, and quality of life over 48 weeks as assessed by patient completed questionnaires
- HIV-1 RNA  $\geq 50$  c/ml (confirmed on a separate sample within 1 week) at any time throughout follow up
- HIV-1 RNA  $< 50$  c/ml at 96 and 144 weeks.
- Adherence over the duration of the trial, as assessed by patient completed questionnaires.
- Change in CD4 (absolute and percentage) from randomisation to 96 and 144 weeks.
- 

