### **Long term follow up:**

The long-term impact of SCT in HIV-1 infected young people is unknown. Following the young people enrolled in BREATHER for two years after the main trial is complete will provide valuable data on the long-term effects of taking weekends off treatment compared to continuous treatment, and whether there is any long-term impact on subsequent disease progression and efficacy of future treatment.

Routine clinical data will be collected (see flowsheet 1.13) and 12-16 weekly HIV-1 RNA viral load monitoring will be funded for participants in both arms where this is not standard of care at the participating centre. Management of HIV-1 RNA viral load should continue as specified in appendix 15.

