## 2.6 Risks and benefits

The potential risks of the SCT strategy are:

- The main risk is that the SCT strategy will prove ineffective in maintaining viral suppression, either because viral load cannot be maintained below detection levels during 2 days off ART, or due to non-adherence to the strategy by extending the time off treatment. However, if a raised viral load is confirmed on repeat testing (to be done within 1 week) then the participant will be placed back on continuous therapy.
- An additional risk is that young people, who have been fully adherent to ART prior to enrolment in the study, might extend the permitted very short interruptions and that overall adherence could decline. Of note, there is equipoise about whether adherence would be better or worse in the SCT arm compared with the continuous therapy arm as young people in the continuous arm may also not take their treatment regularly. All young people will be given diaries to record when they have taken ART and will be asked to comment about difficulties in remembering to take medication.  
Rebounding viral load comes with the risk of development of resistance (particularly to EFV and 3TC which have low genetic barriers to resistance) and which in turn may limit future therapeutic options. Resistance testing will be performed on all young people who lose virological suppression in either arm at the point of loss of suppression ( $\geq 50$  c/ml), as well as on any subsequent samples with HIV-1 RNA  $\geq 1000$  copies/ml.

The potential benefits of the SCT strategy are:

- Improvement in quality of life by having weekends free from taking medication.
- Improved long-term adherence during the week.
- Decreased long-term toxicity to antiretroviral drugs (particularly relevant for some NRTI drugs e.g. ZDV and TDF).
- Decreased cost which is important to any healthcare service, and in particular for many parts of the world where HIV prevalence is highest.

Young people and carers will be fully informed of possible benefits and known risks by means of a patient information sheet as appropriate and this will be reinforced by discussions with the study research teams at the individual sites prior to enrolment.

Data from the pilot phase have been reviewed by the IDMC who identified no safety concerns and recommended that recruitment continue.

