# **5 SELECTION OF YOUNG PEOPLE**

## **5.1 Inclusion criteria**

- HIV-1 infected young people aged 8 to 24 years inclusive (Young people recruited between the ages of 16-24 must either be in regular physical contact with their clinician or be able to transfer to an adult physician at the same site for follow-up or to an affiliated adult site).
- Parents/carers and/or young people, where applicable, willing to provide informed consent.
- On a stable first-line ART treatment containing at least 2 NRTIs/NtRTIs and EFV for at least 12 months and willing to continue the regimen throughout the study period. Young people on regimens containing nevirapine (NVP) or a boosted protease inhibitor with undetectable viral load for over one year who wish to enrol should switch to EFV. Once they are stable on the EFV containing regimen for more than 12 weeks they may be enrolled (must have 2 subsequent HIV-1 RNA measurements <50 c/ml over a minimum period of 12 weeks). Previous dual therapy and/or substitution of NRTIs is allowed providing any changes were not for disease progression, immunological or virological failure (where virological failure is defined as two successive HIV-1 RNA results >1000 c/ml) subsequent to virological control having been achieved on ART.
- Viral suppression (HIV-1 RNA <50 c/ml) for at least the prior 12 months (at least the last 3 measurements, including screening): young people who have experienced a single viral load >50 but <1000 copies/ml (preceded and followed by VL<50 c/ml) in the last 12 months can be enrolled.
- CD4 cell count  $\geq 350 \times 10^6/L$  at screening visit.
- Centre must routinely use an assay which detects HIV RNA-1 viral load  $\geq 50$  c/ml.

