### 8.5 Cells and Plasma for storage

6ml of EDTA blood will be collected throughout the trial for plasma storage for viral load testing and analyses as part of the virology/immunology substudy (Appendix 11), and other HIV related tests as appropriate. Plasma will be stored at weeks -4 to -2 (screening), week 0 (randomisation), 4, 8 (pilot only), 12, 24, 36 and 48 from all participants in both arms. Plasma will also be stored at weeks 1, 2 and 3 for participants in the pilot phase. (See flowsheets)

In addition, in centres who have capability, cells from all participants will be stored at weeks -4/-2 (screening), 0, 4, 12, 24, 48 and every 24 weeks until the end of the trial at  $-80^{\circ}\text{C}$  for subsequent assessments as part of the virology/immunology substudy (see Appendix 11). An extra 10ml of whole blood is required at the time points for cell storage.

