## **APPENDIX 11: VIROLOGY/IMMUNOLOGY SUBSTUDY**

### **Virology**

Proviral DNA will be quantified in all young people at randomisation (week 0) to ascertain whether it can predict response in both arms. To determine whether proviral DNA load differs between arms it will be assayed again in all young people at 48 weeks, and in young people in the SCT arm at 4 weeks. Low level viral loads (<10 c/ml) will also be carried out at the same time points, as well as in young people in the pilot phase of the SCT arm will also be assayed at phlebotomy visits at week 1, 2 and 3 (Monday after interrupting therapy on Saturday/Sunday).

Resistance testing will be performed on all young people who lose virological suppression in either arm at the point of loss of suppression ( $\geq 50$  c/ml), and any subsequent samples with HIV-1 RNA  $\geq 1000$  c/ml. Resistance tests will be performed locally; where this is not possible or the amino acid sequence in FASTA file format cannot be provided, they will be performed centrally.

Therefore, samples will be used to determine if differences in proviral DNA during the study correlate with virological outcome and whether SCT will reduce the subsequent drug options through increased number of drug resistant mutations emerging during the study.

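### The resistance outcome counts mutations present, not newly emerged, and closes at week 48 although SCT exposure and genotyping continue

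*Combined protocol and SAP*

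**What the plan says.** The outcome appears with the same content in protocol sections 1.4, 4.2 and 11.2: "Number of HIV mutations present at week 4, 12, 24, 36 or 48 conferring resistance to drugs taken at randomisation or during the trial".

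The purpose is given in Appendix 11, which wants to know whether SCT will reduce later drug options through an "increased number of drug resistant mutations emerging during the study".

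On who is genotyped, Appendix 11 states: "Resistance testing will be performed on all young people who lose virological suppression in either arm at the point of loss of suppression" (50 c/ml or more). Sections 2.6 and 13.2 give the same rule. Section 2.6 adds testing "as well as on any subsequent samples with HIV-1 RNA" of at least 1000 c/ml, with no week limit.

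On entry, section 5.1 requires "Viral suppression (HIV-1 RNA <50 c/ml) for at least the prior 12 months". It also says "Previous dual therapy and/or substitution of NRTIs is allowed", provided the changes were not made for disease progression or for immunological or virological failure. Section 5.2 excludes earlier monotherapy except for prevention of mother-to-child transmission. No entry or historical genotype is listed in the eligibility criteria, the screening or week 0 procedures, or the flowsheets. Appendix 11 has proviral DNA quantified at week 0 and does not mention sequencing it.

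On stored material, section 8.5 has plasma stored for everyone at screening and week 0. At centres able to do so, "cells from all participants will be stored at weeks -4/-2 (screening), 0, 4, 12, 24, 48". Section 8.4 plans resistance testing on stored samples without saying which.

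On the longer term, section 1.6 wants to learn "whether there is any long-term impact on subsequent disease progression and efficacy of future treatment". The outcomes reaching past week 48 include confirmed rebound at any time, and suppression and CD4 change at weeks 96 and 144. None concerns resistance.

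**The concern.** Two mismatches stand out.

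First, a mutation found at rebound may have arisen on trial or may have been there at entry. Without an entry comparison the two look the same. Carriage at entry is balanced by randomisation, but detection needs both carriage and rebound, and rebound is what the strategy may change. If SCT has more rebounds, it will tend to show more mutations even if none emerged. Because the outcome counts mutations and not participants, one carrier of several old mutations weighs more than one participant with a single new one.

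Second, week 48 cuts off data that the trial will collect. Under section 1.6 recruitment lasts 27 months and SCT participants stay on the strategy until the last participant reaches week 48. Taking 27 months as 27 × 52/12 = 117 weeks, the earliest recruits could have up to about 117 + 48 = 165 weeks on SCT within the main trial. Resistance found after week 48 bears directly on future drug options, which sections 2.6 and 13.2 name as the risk, yet it enters no listed comparison.

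**Working it through.** **The plan's own figure.** Section 11.3 gives no figure for resistance, so the check starts from the primary sample size. With 90% suppressed in both arms, a margin of 0.12, one-sided alpha 0.05 and 80% power:

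n per arm = (1.645 + 0.842)² × (2 × 0.90 × 0.10) / 0.12² = 77.3, or 154.6 in total.

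The plan states 155, which agrees. The suppression rates and the minimum of 80 per arm are used below.

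**How many are genotyped (expected, to week 48).** Arm size × proportion losing suppression:

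- Planning assumption, 10% in each arm: 80 × 0.10 = 8 per arm (95% binomial range 3 to 14), 16 in total.
- SCT at the margin, 22% against 10%: 80 × 0.22 = 17.6 and 80 × 0.10 = 8, 25.6 in total.
- Same scenario at the maximum of 220: 110 × 0.22 + 110 × 0.10 = 24.2 + 11 = 35.2.

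**Old mutations revealed when none emerge.** Let q be the proportion carrying a countable mutation at entry. The documents give no value, so 5% to 20% is assumed, equal in both arms, unrelated to rebound, with every genotype successful. Expected carriers revealed = arm size × rebound × q.

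| q (assumed) | SCT, 22% rebound | Continuous, 10% rebound | Difference |
|---|---|---|---|
| 5% | 0.88 | 0.40 | 0.48 |
| 10% | 1.76 | 0.80 | 0.96 |
| 20% | 3.52 | 1.60 | 1.92 |

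At equal rebound the difference is 80 × 0.10 × q − 80 × 0.10 × q = 0 for every q. Using all randomised as the denominator does not remove the difference in the table, because the counts are already per 80 randomised. Only a comparison with entry removes it.

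**Chance differences at equal rebound.** With exactly 8 genotyped per arm, if 10%, 25% or 50% of them carried an old mutation (assumed), the arms would differ by two or more carriers by chance with probability 19%, 38% or 45%.

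**How much the comparison can show.** At 80 per arm, a two-sided Fisher exact test needs at least 6 against 0 participants for p ≤ 0.05. The top row of distortion, rounded to 4/80 against 2/80, gives p = 0.68.

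**The case against.** The strongest reply is that randomisation balances entry mutations, the analysis is by intention to treat, and the testing trigger is the same in both arms. That stands, and it limits the problem to a detection effect that exists only when rebound differs. A reader might infer that the outcome cannot show whether SCT causes resistance at all. The documents do not support that: a comparison over all randomised still estimates the effect of SCT on resistance detected. What it cannot do is divide that effect into emergence and unmasking.

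A reader might also infer that old mutations could dominate the result. This is not shown. The excess is at most about two participants in the range examined, it rests on an assumed carriage, and there is no estimate of emergent mutations to set against it. The entry criteria also restrain carriage: regimen changes for failure are barred, at least 12 months of suppression is required, and mutations affecting only abandoned drugs are not counted. The bar on virological failure does, however, refer to failure after control had been achieved, so earlier incompletely suppressive therapy is not clearly excluded.

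It may be tempting to fault genotyping only viraemic participants. Everyone enters below 50 c/ml, where a plasma genotype is not expected to be obtainable (an assumption), so the restriction is largely unavoidable.

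Three further points have some force. Section 8.4 leaves room for entry testing on stored samples, so it is unspecified, not ruled out. Late virological outcomes cover part of the question on future treatment, though they do not show which drugs were lost. Section 11.6 defers detail to a separate SAP, whose text is not in the document supplied; it may contain handling rules, but the protocol's outcome wording and its week-48 limit would remain.

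**Conclusion.** The point holds in a limited form. The outcome counts mutations present, the stated question is about mutations emerging, and no entry comparator is specified. It therefore cannot separate emergence from unmasking if rebound differs between arms. The expected size is zero under the plan's own 90%/90% assumption, and about 0.5 to 1.9 participants per 80 at 22% against 10% rebound with 5% to 20% carriage. That range assumes equal carriage by arm, no link between carriage and rebound, and successful genotyping. If carriers rebound more readily, the figures would be larger by an amount the documents do not allow one to calculate.

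The week-48 limit holds without any such assumption. Testing and exposure continue, the long-term aim depends on them, and no resistance outcome uses the results.

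This concerns one secondary outcome and leaves the primary analysis untouched. It is worth changing because the change is cheap and lets the trial answer its own question.

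**What to change.** 1. Extend the resistance outcome from weeks 4–48 to all follow-up, using the genotypes that Appendix 11 already requires. This matches the existing any-time rebound outcome and the 96- and 144-week outcomes. The week-48 result can be kept as a separate line.

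2. In the SAP, analyse the number of participants with at least one major mutation on the IAS-USA list (section 11.6) against drugs taken at randomisation or during the trial, over all randomised. Count participants who were never viraemic as having none observed. State how viraemic participants with no usable genotype are counted.

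3. Report any and new mutations side by side. New means absent on a historical genotype or, where cells were stored, on a screening or week 0 sample. Entry samples need testing only for participants with an on-trial mutation.

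The cost is a change of wording plus a few retrospective genotypes. To week 48 these are a subset of the 16 to 26 participants expected to be genotyped at 160 enrolled, or of about 35 in the margin scenario at 220. The longer window adds some that cannot be counted in advance. Centres with neither stored cells nor a historical genotype will leave some cases unclassifiable, to be reported separately. Treatment, visits and sampling do not change.

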## **4.3 Data collection and handling**

Data will be recorded on CRFs; the top copy/original (or a scan of the original) should be sent to the appropriate Trials Unit for data entry and a copy kept at the local clinical centre. The type of data to be recorded is detailed in the Assessments and Follow up section (section 8). Data from the CRFs will be entered onto databases held at the co-ordinating Trials Units, and exported into Stata for analysis. After completion, adherence and acceptability questionnaires should be sent to the appropriate Trials Unit for data entry.

# **5 SELECTION OF YOUNG PEOPLE**

## **5.1 Inclusion criteria**

- HIV-1 infected young people aged 8 to 24 years inclusive (Young people recruited between the ages of 16-24 must either be in regular physical contact with their clinician or be able to transfer to an adult physician at the same site for follow-up or to an affiliated adult site).
- Parents/carers and/or young people, where applicable, willing to provide informed consent.
- On a stable first-line ART treatment containing at least 2 NRTIs/NtRTIs and EFV for at least 12 months and willing to continue the regimen throughout the study period. Young people on regimens containing nevirapine (NVP) or a boosted protease inhibitor with undetectable viral load for over one year who wish to enrol should switch to EFV. Once they are stable on the EFV containing regimen for more than 12 weeks they may be enrolled (must have 2 subsequent HIV-1 RNA measurements <50 c/ml over a minimum period of 12 weeks). Previous dual therapy and/or substitution of NRTIs is allowed providing any changes were not for disease progression, immunological or virological failure (where virological failure is defined as two successive HIV-1 RNA results >1000 c/ml) subsequent to virological control having been achieved on ART.
- Viral suppression (HIV-1 RNA <50 c/ml) for at least the prior 12 months (at least the last 3 measurements, including screening): young people who have experienced a single viral load >50 but <1000 copies/ml (preceded and followed by VL<50 c/ml) in the last 12 months can be enrolled.
- CD4 cell count  $\geq 350 \times 10^6/L$  at screening visit.
- Centre must routinely use an assay which detects HIV RNA-1 viral load  $\geq 50$  c/ml.

## **5.2 Exclusion criteria**

- Pregnancy or risk of pregnancy in females of child bearing potential.
- Acute illness (young people may be enrolled after illness).
- Receiving concomitant therapy for an acute illness (young people may be enrolled after finishing therapy).
- A creatinine, AST or ALT of grade 3 or above at screening.
- On a regimen including nevirapine or a boosted PI (young people may switch to an EFV based regimen).
- Previous ART monotherapy (except for the prevention of mother-to-child transmission)

## **5.3 Siblings**

If more than one child from the same family is eligible and carers give consent to enrolment into the trial, they will be enrolled to the same arm of the study in order to avoid problems caused by one sibling taking weekend breaks and not the other. Please indicate this in the relevant section of the randomisation form. (See section 11.1).

## **5.4 Co-enrolment guidelines**

Co-enrolment in compatible studies is allowed by the protocol but must first be approved by the Trials Unit. Centres should also adhere to local guidelines concerning co-enrolment in other trials.

## **5.5 Number and source of young people**

It is planned to recruit a minimum of 160 young people from clinical centres in countries participating in the PENTA, PHPT and HIV-NAT networks (Thailand), a centre in Uganda, a centre in the USA and a centre in the Ukraine.

## 6 ENROLMENT AND RANDOMISATION

### 6.1 Screening procedures and pre-randomisation investigations

#### 6.1.1 Enrolment and consent

Enrolment will not start until each centre has received ethics and regulatory approval or approvals are imminent.

All participants and parent/carers will be given information about the objectives and rationale of the study and the possible risks (see sample patient information sheets in Appendix 1) unless the participant is unaware of their diagnosis; in this case only the parent/carer need be given the information sheet. Potential participants and parents/carers can consider entry into the trial for a longer period of time if necessary, if the participant continues to meet the eligibility criteria.

Young people should be assessed for entry to the trial based on the eligibility inclusion and exclusion criteria (see section 5.1 and 5.2) and if it is anticipated that HAART could be stopped for two days every week at the next clinic visit in 2-4 weeks' time.

Written informed consent to enter the trial must be obtained from participants and/or parents/carers (including legal authorities) as appropriate after explanation of the aims, methods, benefits and potential hazards of the trial and BEFORE any trial specific procedures are performed (see sample consent form in Appendix 2). All children who are deemed competent by the clinician and are aware of their HIV diagnosis will be given an age-specific information sheet (see Appendix 1) and asked to sign an assent form (see Appendix 2). If the participant is not aware of their diagnosis they will not be asked to give assent. For adolescents, consent should be obtained according to national regulations.

It must be made completely and unambiguously clear to parents and participants that they are free to refuse to participate in the trial, or withdraw their consent at any time and for any reason, without affecting their routine treatment. The signed informed consent form must be kept in the trial site file with a copy in the patient's medical records and one given to the family/participant (or as per local requirements). With the parents' and/or participant's consent, a letter should be sent to the participant's GP informing him/her of the trial and the young person's involvement in it (see Appendix 3).

